### Outcomes

As indicated above, the ASAP questionnaire represents the outcome of interest for study Part A. For study Parts B and C, eight assessments are planned: at baseline prior to the RCT (T1), as well as weekly during the RCT (T2–T5) and the crossover study (T6–T8). Each survey will include an assessment of basic information (e.g., sex and age) and brief questions assessing general psychological and physical well-being. Additionally, a battery of questionnaires will be applied. The components were chosen based on both, thorough psychometric evaluation and the availability of translation and cross-cultural validation for the languages used. Implemented tools include the WHO5 scale for mental well-being (16, 17), generalized anxiety disorder scale-7 [GAD-7, (22)] for impulsiveness and anxiety, the MOS 12-item scale for sleep quality (23), the self-concordance scale (24) for exercise motivation and the Chronic Graded Pain Scale (25) for pain. In addition to the intervention effects, data on acceptance and adherence will be collected by means of documenting attendance at each workout offered in study Part B as well as by means of asking for the frequency of database use in study Part C (T4 assessment).

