### Data Processing and Statistics

All datasets will be analyzed using intention-to-treat. The findings from the ASAP questionnaire (Study Part A) will be descriptively reported and presented using appropriate measures such as mean ± standard deviation or median and interquartile range depending on distributions and scales of measurement. Additionally, the significance of variable associations (e.g., between physical activity levels and markers of well-being) will be examined using correlation and regression analyses.

To estimate the risk of non-response bias, wave analyses will be conducted according to Lewis et al. (26). Specifically, the responses of the first 10% percent of the participants (early responders) will be compared to those of the last 10% (late responders) by means of inferential statistics. The rationale behind this is that early responders are assumed to be more motivated than late responders which can be compared to non-responders. Hence, if the wave analyses do not provide significant findings, absence of non-response bias is concluded.

For study Parts B and C (randomized, controlled trial/controlled crossover trial), a prospective meta-experiment approach will be applied (27). For each country, the mean pre-post-differences between-groups including 95% confidence intervals (95% CI) will be calculated at the different time points. An a priori sample size calculation using an algorithm specifically designed to account for between-site variance in multi-center trials was performed (28). When achieving a sample size of *n* = 544 with an included drop-out rate of 20%, the trial will have 80.3% power to detect pre-post-differences with a minimal effect size (Cohen's *d*) of 0.25 at an alpha level of 0.05. To account for potential between-center variance, the data collected in each country will be pooled using a random-effects model (29). This leads to an aggregated effect size (weighted mean differences) demonstrating the overall effectiveness of the intervention while the different countries can still be compared by means of inspecting the 95% CI's. Heterogeneity between countries will be quantified by means of the *I*^2^ index (30). To further explore its potential sources (e.g., country, age, sex, baseline physical activity), a meta-regression with continuous and factorial independent variables will be performed (31).

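### As the plan reads, effect moderators are explored by meta-regression on one effect per country: country then cannot be tested as a factor, and age, sex and baseline activity enter only as country averages

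*Protocol article*

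**What the plan says.** Under Data Processing and Statistics, the protocol article sets out a two-stage analysis for Parts B and C.

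- Stage one: "For each country, the mean pre-post-differences between-groups including 95% confidence intervals (95% CI) will be calculated at the different time points".
- Stage two: "the data collected in each country will be pooled using a random-effects model".
- Reading across countries: "the different countries can still be compared by means of inspecting the 95"% confidence intervals (CIs).
- Heterogeneity: "Heterogeneity between countries will be quantified by means of the" I-squared index.
- Sources of heterogeneity: "To further explore its potential sources (e.g., country, age, sex, baseline physical activity), a meta-regression" with continuous and factorial variables.

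The same section sets the significance level for all analyses at 0.05. It does not say how many countries are expected, at what level the covariates enter, or what pattern of CIs would count as a difference. The Outcomes section shows that age and sex are held for each participant: "Each survey will include an assessment of basic information (e.g., sex and age").

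**The concern.** The plan moves from country effects, to pooling, to heterogeneity between countries, to a regression that looks for the sources of that heterogeneity. In that sequence each data point is a country.

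Two things follow. A factor with one level per country explains the country effects perfectly and tests nothing. Age, sex and baseline activity are traits of persons, but they could enter only as country means or proportions. A slope across countries is not protected by randomisation, because countries with older participants also differ in restrictions, instructors and recruitment. It can differ in size or sign from the relation within countries. The trial holds the individual data that would answer the question directly.

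The secondary issue is the comparison of countries. CI inspection is the only stated way to set one country against another, and it has no defined error rate. At stake are exploratory statements on where and for whom the programme works, in a trial whose abstract expects to inform policy makers.

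**Working it through.** **Inputs**
- From the article: "When achieving a sample size of *n* = 544 with an included drop-out rate of 20"%, so 544 × 0.8 = 435 completers; d = 0.25; alpha 0.05; 1:1 allocation.
- Assumed: number of countries K = 7, range 4 to 14 (not stated; seven questionnaire languages is the only related figure).
- Assumed: share s of a covariate's variance lying between countries, 2% to 10%.
- Assumed: equal country sizes and outcome SD = 1.

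**The plan's own figure.** The article gives no figure on moderators or country comparisons. Its 80.3% power is not matched by a plain two-group calculation (two-sided 83.0% with 544, 74.1% with 435; one-sided 89.8% and 83.2%). The between-site inputs of its algorithm are not given, so this does not show an error, and nothing below depends on it.

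**1. Country as a factor.** K effects, less an intercept and K − 1 dummies: K − (1 + K − 1) = 0 residual degrees of freedom, for any K.

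**2. Few data points for the other covariates.** An intercept and three slopes (age, sex, baseline activity) leave K − 4 residual degrees of freedom: 0 at K = 4, 3 at K = 7, 10 at K = 14.

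**3. Precision lost by averaging.** With N participants and covariate variance V:
- slope across country means: variance ≈ 4 / (N·s·V);
- within-country treatment-by-covariate interaction: variance ≈ 4 / (N·(1 − s)·V);
- ratio of standard errors = √((1 − s)/s).

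| s (assumed) | SE ratio |
|---|---|
| 2% | √(0.98/0.02) = 7.0 |
| 5% | √(0.95/0.05) = 4.4 |
| 10% | √(0.90/0.10) = 3.0 |

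The ratio does not depend on K. It leaves out residual between-country variance, which would widen the across-country slope further, and it says nothing about bias.

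**4. Inspecting country CIs, one pair with equal standard errors.**
- If the rule is non-overlap: z = 2 × 1.96/√2 = 2.77, two-sided p = 0.0056. A comparison with 80% power by a direct test has 51% under this rule.
- If the rule is that one estimate lies outside the other's CI: z = 1.96/√2 = 1.39, p ≈ 0.17.

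The error rate therefore depends on a rule that the article does not state.

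**5. Many pairs.** Simulating equal true effects, the chance that at least one pair of CIs fails to overlap is about 3% (K = 4), 8% (K = 7), 15% (K = 10) and 24% (K = 14).

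**6. Scale at K = 7.** 435/7 ≈ 62 per country; SE = 2/√62.2 = 0.254; CI half-width 1.96 × 0.254 = 0.50 SD. Non-overlap needs an observed gap of 0.99 SD; a direct test needs 1.96 × √2 × 0.254 = 0.70 SD.

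**The case against.** The strongest reply is that the article fixes little of this.

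- **Covariate level.** The article does not say that covariates enter as country means. That stands. A reader might infer that moderator effects will be ecologically confounded; the text supports only a risk of ecological bias under the natural reading.
- **One effect per country.** Estimates are planned at several time points, and the trial is called multicentre, so country need not be saturated. This stands only in part. Repeated time points from one country are not independent units. The article deals with between-centre variance by pooling per country, so it defines no lower-level effects that would free degrees of freedom.
- **No overlap rule.** The article says only that CIs will be inspected. A reader might infer that countries will be judged by overlap and that real differences will therefore be missed. The documents do not support this. No rule is stated, and I-squared and meta-regression are also planned. At K = 7 the smallest pairwise difference with 80% power is about 1.0 SD by a direct test and 1.3 SD by non-overlap (0.76 to 1.42 and 0.98 to 1.83 for K = 4 to 14). Both are far above the target of 0.25, so the main limit is the number per country. Over many pairs the larger risk may be false differences.
- **Detail left to a fuller document.** A Q test or tau-squared may be specified elsewhere, and their absence is not the complaint. The complaint is that the stated methods, as they read, do not suit the stated covariates or comparison.
- **Exploratory status.** The article introduces the meta-regression as exploration, with covariates given as examples. That stands and limits the severity.

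**Conclusion.** The point holds, at minor to moderate severity. If the country is the unit, as the sequence of the analysis implies, country as a factor cannot be tested. For age, sex and baseline activity the planned analysis would be inefficient, with a standard error about 3 to 7 times that of a within-country interaction when 10% to 2% of covariate variance lies between countries, and it would be open to ecological bias. The saturation result needs only one effect per country. The standard-error ratio rests on the assumed variance share and on equal country sizes.

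Inspecting country CIs is a secondary weakness: it is not a test at 0.05, and its error rate is undefined until a rule is named. The figures in SD units depend on an assumed number of countries.

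A reader might also infer that the main result is compromised. It is not: the randomised contrasts within countries and their pooled effect do not depend on either step.

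**What to change.** Change the analysis wording as follows.

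1. For age, sex and baseline physical activity, estimate participant-level treatment-by-covariate interactions with covariates centred within country, either in a one-stage mixed model or by pooling the within-country interactions. For baseline activity this presumes a participant-level measure at baseline in Part B; the Part A survey is anonymous and could not supply it.
2. Keep meta-regression only for true country-level covariates, such as a measure of how strict public restrictions were, and drop country from its covariate list.
3. Base statements on country differences on one global treatment-by-country heterogeneity test, with tau-squared and its CI beside I-squared. Label the country CIs descriptive.

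The global test will itself be weak: at K = 7 with 435 completers, simulated power is about 26% for a between-country SD of 0.2 and 51% for 0.3. A non-significant result should therefore not be read as homogeneity, which is why the interval for tau-squared matters.

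The cost is a few sentences and modest programming. No new data are needed beyond the baseline activity measure that the plan already presupposes.

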## Abstract

**Introduction:** The worldwide spread of the novel coronavirus (SARS-CoV2) has prompted numerous countries to restrict public life. Related measures, such as limits on social gatherings, business closures, or lockdowns, are expected to considerably reduce the individual opportunities to move outside the home. As physical activity (PA) and sport participation significantly contribute to health, this study has two objectives. The objectives of this study are to assess changes in PA and well-being since the coronavirus outbreak in affected countries. Additionally, we will evaluate the impact of digital home-based exercise programs on PA as well as physical and mental health outcomes.

**Method:** A multinational network trial will be conducted with three planned phases (A, B, and C). Part A consists of administering a structured survey. It investigates changes in PA levels and health during the coronavirus outbreak and measures the preferences of the participants regarding online training programs. Part B is a two-armed randomized-controlled trial. Participants assigned to the intervention group (IG) will complete a digital 4-week home exercise training (live streaming via internet) guided by the survey results on content and time of program. The control group (CG) will not receive the program. Part C is 4-week access of both CG and IG to a digital archive of pre-recorded workouts from Part B. Similar to Part A, questionnaires will be used in both Part B and C to estimate the effects of exercise on measures of mental and physical health.

**Results and Discussion:** The ASAP project will provide valuable insights into the importance of PA during a global pandemic. Our initial survey is the first to determine how governmental confinement measures impact bodily and mental well-being. Based on the results, the intervention studies will be unique to address health problems potentially arising from losses in PA. If proven effective, the newly developed telehealth programs could become a significant and easy-to-distribute factor in combating PA decreases. Results of the study may hence guide policy makers on methods to maintain PA and health when being forced to restrict public life.

**Study Register:** DRKS00021273.

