Data analyses will be performed using standard statistical software packages (e.g., SPSS 22, SPSS Inc., Chicago, Illinois, USA and BiAs statistics, Goethe University, Frankfurt/Main, Germany). The significance level for all analyses will be set to α = 0.05.

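### The plan measures between-country heterogeneity only by I², which does not say how far country effects differ; τ with a confidence interval and a prediction interval are needed

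*Protocol article*

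**What the plan says.** All of the following is in the Protocol article, Data Processing and Statistics, unless another section is named.

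- **Country estimates.** "For each country, the mean pre-post-differences between-groups including 95% confidence intervals (95% CI) will be calculated at the different time points".
- **Pooling.** The country estimates are combined in a random-effects model. "This leads to an aggregated effect size (weighted mean differences) demonstrating the overall effectiveness of the intervention".
- **Heterogeneity.** "Heterogeneity between countries will be quantified by means of the" I² index. The text names no between-country SD or variance, no interval for heterogeneity and no prediction interval.
- **Other between-country tools.** Countries are compared by looking at their 95% CIs, and a meta-regression explores possible sources of heterogeneity.
- **Size.** The target is 544 participants, "with an included drop-out rate of 20%, the trial will have 80.3% power to detect pre-post-differences" with a Cohen's d "of 0.25 at an alpha level of 0.05". Neither the number of countries nor the number per country is given.
- **Intended use.** The Abstract says: "Results of the study may hence guide policy makers on methods to maintain PA and health".

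**The concern.** I² is the fraction of the observed variation between country estimates that sampling error does not explain. It is not the amount by which the effects differ. The same spread of true effects gives a small I² when countries are small and a large one when they are big. With a few hundred participants divided among several countries, sampling error dominates and I² is pulled towards zero.

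This matters here because the workouts can be modified locally (Study Part B), so real differences between countries are plausible, and because the results are meant to inform policy. A policy maker needs to know how much the effect may vary and what might be expected in a country outside the trial. I² answers neither question, and nor does a confidence interval for the pooled mean.

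**Working it through.** **The plan's own figure.** The plan gives no numerical heterogeneity figure to reproduce. Its one related number, 80.3% power, could not be reproduced with a simple two-sided comparison of two means. That gives 83.0% with all 544 and 74.1% with 544 × 0.8 ≈ 435. The cited multi-centre algorithm's inputs are not given, so this does not show an error, and nothing below depends on it.

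**Inputs from the article.** N = 544, or about 435 after 20% drop-out; 1:1 allocation (Study Part B); target d = 0.25, so SD = 1 on this scale.

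**Assumptions, not in the article.**
- K = 5 to 15 countries of equal size.
- τ = 0.125, which puts true effects at 0.25 ± 2 × 0.125, or 0 to 0.5.
- τ = 0.15, which puts them at 0.25 ± 1.96 × 0.15, or −0.04 to 0.54.

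**Step 1: dependence on country size.** With n per country and n/2 per arm, the variance of a country's effect is v = 2/n + 2/n = 4/n, and the typical I² is τ²/(τ² + v). For τ = 0.15:
- n = 40: 0.0225/(0.0225 + 0.100) = 18%.
- n = 200: 0.0225/(0.0225 + 0.020) = 53%.

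The spread is identical and the readings are very different.

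**Step 2: how often I² reads 0%.** I² is set to zero when Cochran's Q ≤ K − 1. With equal sizes, Q is distributed as (1 + τ²/v) times a χ² with K − 1 degrees of freedom. So P(I² = 0) = P(χ²(K−1) ≤ (K − 1)/(1 + τ²/v)). Example with N = 435, K = 10, τ = 0.15: v = 4 × 10/435 = 0.0920, τ²/v = 0.245, and P(χ²(9) ≤ 9/1.245) = 0.387.

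**Step 3: what a zero reading leaves open.** With equal sizes, the Q-profile 95% upper limit for τ is the square root of v × (Q/χ²(0.025; K−1) − 1). The table evaluates it at Q = K − 1, where I² just reads 0%. The half-width of a single country's 95% CI is 1.96√v.

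| N | K | v | Typical I², τ = 0.15 | P(0%), τ = 0 | P(0%), τ = 0.125 | P(0%), τ = 0.15 | Upper limit for τ | Country CI half-width |
|---|---|---|---|---|---|---|---|---|
| 544 | 5 | 0.037 | 0.380 | 0.594 | 0.409 | 0.352 | 0.517 | 0.376 |
| 544 | 10 | 0.074 | 0.234 | 0.563 | 0.407 | 0.352 | 0.414 | 0.531 |
| 544 | 15 | 0.110 | 0.169 | 0.550 | 0.415 | 0.364 | 0.405 | 0.651 |
| 435 | 5 | 0.046 | 0.329 | 0.594 | 0.440 | 0.388 | 0.578 | 0.420 |
| 435 | 10 | 0.092 | 0.197 | 0.563 | 0.435 | 0.387 | 0.463 | 0.594 |
| 435 | 15 | 0.138 | 0.140 | 0.550 | 0.440 | 0.397 | 0.453 | 0.728 |

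Over K = 5 to 15, zero readings occur in 35–44% of trials with real heterogeneity and in 55–59% with none. A zero is therefore only 1.25 (0.550/0.440) to 1.7 (0.594/0.352) times as likely under identical effects. When I² just reads 0%, the upper limit for τ is about 0.41–0.58, above the target effect of 0.25. It is lower when Q is smaller: at Q = (K − 1)/2 it is 0.18–0.38 for K = 5 to 14.

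**Step 4: sensitivity.**
- Unequal sizes (5:1 gradient), N = 435, τ = 0.15, K = 5 to 14: about 39–40% zeros, essentially unchanged.
- Fixed effects evenly spaced from 0 to 0.5, K = 5 to 20: 20–36% zeros at N = 544 and 26–39% at N = 435. With K = 3 the figures are 10% and 15%.
- N = 2000, K = 5 to 15: about 11–18% zeros. N = 5000 with τ = 0.125: about 4–6%.

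**The case against.** Several points on the other side stand.

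- **The zeros are not peculiar to I².** They come from little information per country. A moment-based point estimate of τ² is zero in exactly the same datasets, so replacing one point estimate with another would gain nothing there. What is specific to I² is that it is not on the effect scale.
- **The country sizes are unknown.** A reader might infer that this trial will often show 0% while effects run from nil to twice the target. The article does not support that as a statement about this trial: the number of countries and τ are assumptions. Nor is 544 a cap. It is the size at which the stated power applies, recruitment is open through social media, and the Discussion expects questionnaires to allow large samples.
- **No misreading is planned.** A reader might also infer that a low I² will be reported as consistent effects. The article sets no I² threshold and no such rule, and the Abstract's remark on policy makers does not claim uniform effects.
- **Other tools are named.** Country CIs are on the outcome scale, and their width would show the imprecision. But half-widths of 0.38–0.73 exceed the target effect, so looking at them does not yield an amount of spread. Meta-regression addresses sources, not amount.
- **Article length.** Estimator details may properly sit in a fuller plan. The point here is narrower: the text commits to I² as the quantification, and that is a stated choice.

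**Conclusion.** The point holds as a secondary-level improvement. The measure chosen to quantify heterogeneity does not measure how far country effects differ, and it changes with country size (18% against 53% for the same τ of 0.15). Under the stated assumptions, a 0% reading would hardly separate identical effects from a spread of about nil to twice the target, so it could not support a claim of similar effects across countries. The frequencies depend on the assumed K, τ and N, and the problem shrinks with much larger recruitment. The I² formula's dependence on country size does not rest on the assumed K or total N.

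It should not be read as a fault in the overall result. The random-effects model already carries between-country variance into the pooled estimate and its CI, and that estimate is not changed by how heterogeneity is described.

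**What to change.** In Data Processing and Statistics, replace I² as the measure of heterogeneity with the between-country SD (τ) on the outcome scale, reported with its 95% CI (Q-profile or profile likelihood). Add a 95% prediction interval for the effect in a new country. Keep I² as a descriptive extra, and state that a low or zero value will not be taken as evidence of consistent effects. A point estimate of τ without its interval would not solve the problem.

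Do not add a consistency rule that only asks for the upper limit of τ to be small relative to the pooled effect. Without a number it is not a rule, and with upper limits of the size shown above it would rarely be met.

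The cost is a change of wording and a few lines of output, with no new data and no design change. The downside is that with few countries both intervals will be wide and the headline less favourable.

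### Part B names no primary scale or time point and sets alpha at 0.05 throughout, so its effectiveness conclusion does not carry the stated 5% error rate

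*Protocol article*

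**What the plan says.** The Outcomes section of the protocol article says that, besides "brief questions assessing general psychological and physical well-being", "a battery of questionnaires will be applied" in Parts B and C. Five scales are named: "WHO5 scale for mental well-being (16, 17), generalized anxiety disorder scale-7" and "the MOS 12-item scale for sleep quality (23), the self-concordance scale (24) for exercise motivation and the Chronic Graded Pain Scale (25) for pain". The list is worded as open, so five is a minimum. Assessments are a baseline (T1), four weekly surveys in Part B (T2 to T5) and three in Part C (T6 to T8).

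Data Processing and Statistics says that, for each country, "the mean pre-post-differences between-groups including 95% confidence intervals (95% CI) will be calculated at the different time points". The country results are then pooled by a random-effects model, and the pooled effect is to show whether the intervention works overall. The same section gives n = 544 (20% drop-out included), 80.3% power, d = 0.25 and alpha 0.05, without saying for which scale or at which assessment. It closes with: "The significance level for all analyses will be set to α = 0.05".

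No primary outcome, primary time point, order of testing or multiplicity adjustment appears in the article.

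**The concern.** The article promises one conclusion, overall effectiveness, but does not say which result decides it. With several scales, several follow-ups and the same 0.05 for each, any of about 20 pooled comparisons could be offered as the evidence. The 5% then describes each comparison, not the conclusion.

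The aims do not supply a default. The abstract speaks of physical activity together with physical and mental health, yet none of the five scales named for Parts B and C measures physical activity. The power statement does not help either, because an effect size of 0.25 on an unnamed outcome cannot be matched to a test.

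This matters because the abstract foresees wide distribution of the programmes and guidance to policy makers if they are shown to work.

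**Working it through.** **The plan's own figure.** The only related figure is the 80.3% power. The standard two-group formula with 1:1 allocation is power = Φ(d·√N/2 − 1.96).
- N = 544 analysed: 0.25 × 23.32/2 − 1.96 = 0.956, so 83.0%.
- N = 544 × 0.8 = 435 completers: 0.25 × 20.86/2 − 1.96 = 0.648, so 74.1%.

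Neither gives 80.3%. The plan used an algorithm that allows for between-site variance, and that variance is not given, so the figure can be neither confirmed nor called wrong. This is a separate matter and does not affect what follows. The article states no family-wise error rate.

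**Inputs from the article.** Five named scales and four post-baseline Part B assessments (Outcomes); 0.05 per analysis (Data Processing and Statistics). Two-sided testing is inferred from the 95% confidence intervals.

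**Assumptions.**
- Each scale is compared at each time point: 5 × 4 = 20 tests.
- There is no true effect on any scale, and each test holds its nominal level.
- Test statistics are normal, with correlation 0 to 0.7 between scales and 0.5 to 0.9 between time points. The article gives no correlations. All scales are coded so that a positive value favours the intervention.

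**Independent tests.**
- Either direction: 1 − 0.95^20 = 0.642.
- In favour of the intervention, 0.025 per test: 1 − 0.975^20 = 0.397.
- T5 only, five tests: 1 − 0.95^5 = 0.226 and 1 − 0.975^5 = 0.119.

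**Correlated tests.** Simulation with 200,000 draws per setting:

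| Tests | Direction | Independent | Correlated, range |
|---|---|---|---|
| 5 scales × T2 to T5 (20) | either | 64.2% | 25.9% to 57.0% |
| 5 scales × T2 to T5 (20) | in favour | 39.7% | 13.0% to 33.4% |
| 5 scales at T5 (5) | either | 22.6% | 14.7% to 22.5% |
| 5 scales at T5 (5) | in favour | 11.9% | 7.4% to 11.8% |
| 6 outcomes × T2 to T5 (24) | either | 70.8% | 28.1% to 63.9% |
| 6 outcomes × T2 to T5 (24) | in favour | 45.5% | 14.0% to 38.6% |

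The low end of the 20-test range has correlation 0.7 between scales and 0.9 over time; the high end has 0 and 0.5. In between, with 0.3 between scales and 0.5 to 0.8 over time, the rate in either direction runs from 54% down to 42%. The rows with six outcomes show the effect of adding one outcome from the brief well-being questions.

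**Comparison.** One scale at one time point gives 5% in either direction and 2.5% in favour. Twenty tests raise the 2.5% to between 13.0/2.5 = 5 and 33.4/2.5 = 13 times that value.

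**The case against.** The strongest reply is that this is a condensed article. The full protocol, an analysis plan or the registry entry may name a primary outcome, and a general significance level does not by itself rule out a hierarchy or a family-wise procedure run at 0.05. The text also does not say that the whole battery is given in every weekly survey. And it describes differences with confidence intervals that "will be calculated at the different time points", which can be read as estimation, not as a test for each scale and week.

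Part of this stands. The count of 20 is an inference and the correlations are assumed, so the error rates are conditional. If only the end of Part B were tested, the T5 rows would apply.

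The rest does not remove the point. A trial protocol normally fixes its primary outcome itself. This article gives sample size, power, effect size and alpha in full yet attaches them to no outcome, and it states one level for every analysis. A later plan with stricter per-test thresholds would have to qualify that sentence.

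Two stronger readings are not supported:
- A reader might infer a 40% to 60% chance of falsely calling the programme effective. Rates of that size arise only when errors in either direction are counted. For the five named scales, the rate in favour of the intervention is 13% to 33%, and just under 40% even with 20 independent tests.
- A reader might add T6 to T8, making 5 × 7 = 35 tests (1 − 0.95^35 = 83% if independent). Under Study Part C both groups have the video database, so those comparisons no longer set the programme against no programme and do not belong in the same family.

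**Conclusion.** The point holds in a conditional form. As written, the plan leaves the Part B effectiveness conclusion without a defined test and without the 5% error rate that the article states. On the natural reading of 20 tests, the chance of at least one false significant difference is about 26% to 57% in either direction and about 13% to 33% in favour of the intervention. If only T5 is tested, it is about 15% to 23% and 7% to 12%.

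These ranges rest on the assumed correlations and the inferred test count. Further outcomes or subscales would raise them, and stronger correlation or fewer tests would lower them. That no scale or time point is singled out, and that the power statement is tied to none, does not depend on those assumptions.

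**What to change.** 1. Name one primary scale at one time point, pooled across countries at two-sided 0.05, as the test of effectiveness. WHO5 at T5 would serve as an example. The article does not rank its outcomes, so the choice is the sponsor's.
2. Tie the 80.3% power and d = 0.25 to that scale and time point.
3. Replace the single 0.05 for every analysis with a family-wise procedure, such as Holm, for the other scales at that time point. With four other named scales, the smallest p-value would be compared with 0.05/4 = 0.0125. If the primary and the other scales are to share one 5% error rate, test the others only after the primary test succeeds.
4. Report the remaining Part B time points and Part C as estimates with 95% confidence intervals, without claims of significance.

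The cost is a change of wording before the between-group data are analysed, and a stricter threshold for secondary claims. The primary test keeps its 0.05, so the multiplicity rule itself does not require a larger sample.
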